## Abstract

**Background:**

Atrial fibrillation (AF) is the most common cardiac arrhythmia. The associated risk of stroke can be effectively reduced by oral anticoagulation; however, these increase bleeding risk or can even be contraindicated. Clinical studies indicate that percutaneous catheter-based left atrial appendage closure (LAAC) may represent an effective alternative for stroke prevention in this high-risk patient group. While the clinical and economic benefits of LAAC have been compared with standard drug therapy indirectly, direct comparisons are lacking, especially for patients with AF at high risk of stroke and bleeding. EvaClosure, a substudy of the CLOSURE-AF-DZHK16 trial, was designed to describe current therapy paths of patients with AF and high risk of stroke and bleeding, while quantifying resource utilization and healthcare costs. Moreover, this study aims to evaluate the health economic impact of LAAC in patients with high risk of stroke and bleeding, compared with the best physician-directed medical therapy (including direct oral anticoagulants when eligible).

**Methods:**

Data gathered in CLOSURE-AF address the effect of different treatment options on health-related quality of life; analyses of resource utilization and healthcare costs are based on claims data from a German statutory health insurance (SHI) provider. Economic information derived from SHI data is complemented by a validated resource use measurement instrument capturing non-medical and indirect costs. The cost–utility analysis uses a Markov model, for which parameters are quantified from statistically matched SHI claims and CLOSURE-AF clinical study data, supplemented by data from the literature.

**Discussion:**

The combination of these databases allows a comprehensive, valid, and policy-relevant assessment of costs and benefits related to LAAC. Moreover, the advantages of the different databases are used for health economic evaluation. The results of this study are expected to generate robust evidence to inform health economic evaluations and provide valuable insights for SHI providers and policymakers on the societal and economic impact of LAAC.

**Clinical Trial Registration:**

ClinicalTrials.gov, Identifier NCT03463317. The clinical study CLOSURE-AF-DZHK16, including the substudy EvaClosure, was registered at ClinicalTrials.gov PRS (Identifier: NCT03463317, Posted: March 13, 2018, Update: July 30, 2021).

## Introduction

1

### Background

1.1

Atrial fibrillation (AF) is the most common cardiac arrhythmia, with the current rate of prevalence ranging between 2% and 4% (1); the prevalence increased in the last 20 years and further augmentations are expected (2, 3). For Germany, current studies have shown a prevalence rate of 3.1% and a significant increase in recent years due to demographic change and a growing awareness of this disease (4, 5). The current estimated lifetime risk of AF at age 55 is 37%, which has also grown in recent years (6, 7). AF increases stroke risk about five-fold, with 15% to 25% of all strokes attributed to AF (8, 9). AF is also associated with a higher risk of mortality (10). In addition to the clinical outcomes, AF causes high economic burden for healthcare systems and society (11, 12), whereby acute care costs of complications contribute substantially to this burden (13). The latest available estimates suggest an economic burden of up to 3.4 billion euros for Germany, primarily due to hospitalizations (14). Because of the increasing prevalence of AF, the associated costs are expected to grow as well (15).

Although non-vitamin K antagonist oral anticoagulants (NOACs) substantially reduce the risk of stroke and systemic embolism in patients with AF, their use in patients with high bleeding risk may be limited by safety concerns and long-term treatment persistence. In pivotal phase III trials and subsequent meta-analyses, the annual rate of incidence of major bleeding during NOAC therapy ranged approximately from 2% to 4%, depending on patient risk profile and drug regimen, with gastrointestinal bleeding representing the most frequent severe bleeding manifestation (16–19). Furthermore, contemporary registry data indicate that persistence with oral anticoagulation declines progressively over time, with discontinuation or non-adherence rates of approximately 15%–30% within the first year of treatment and substantially higher cumulative discontinuation rates during longer follow-up times. The reported reasons include bleeding complications, perceived treatment burden, multimorbidity, drug–drug interactions, and patient preference (10, 20). Consequently, a considerable proportion of patients with AF and high bleeding risk remain undertreated or untreated in routine clinical practice. Current European Society of Cardiology guidelines therefore emphasize the need for individualized stroke prevention strategies and recommend a consideration of left atrial appendage closure in selected patients with contraindications to long-term anticoagulation (21).

Preliminary evidence suggests that percutaneous catheter-based left atrial appendage closure (LAAC) may represent an effective alternative for stroke prevention and may eliminate the need for permanent anticoagulation, especially for patients in this high-risk group (22). However, current research lacks a direct comparison of LAAC with NOAC therapy at a larger scale since this high-risk patient group is often not represented comprehensively in clinical studies. Therefore, additional evidence based on comparative studies is needed to recommend LAAC for routine clinical practice (23).

The CLOSURE-AF-DZHK16 study addresses this research gap. CLOSURE-AF is a prospective, randomized clinical trial involving 42 study centers in Germany^1^ that analyzes the clinical benefit of LAAC in patients with non-valvular AF (NVAF) at high risk of stroke and bleeding (high-risk group)^2^ compared with best physician–directed medical care (including anticoagulation, when tolerated). Patient enrollment began in February 2018, with a study completion date in November 2024. Subjects were randomized 1:1 in the intervention and control group, receiving either catheter-interventional LAAC with a CE-certified LAA occluder (e.g., Watchman™, Amplatzer Amulet) or physician-directed best medical care [NOACs or vitamin K antagonists (VKA), antiplatelet therapy, no antithrombotic/antiplatelet therapy in case of contraindications] chosen at the discretion of the treating physician (23).

Changing standard care by introducing a novel medical device must be supported by evidence of both clinical and economic benefits. However, evidence on LAAC cost-effectiveness in high-risk patients is lacking. Therefore, an incremental analysis of the costs and benefits of the intervention compared with standard medical therapy is essential to adequately reflect its utility for patients as well as the economic impact from the perspectives of both SHI and society. Previous health economic evaluations of LAAC (25–32) predominantly considered patients with NVAF without accounting for contraindications to (N)OACs. All but one of the eight studies evaluated LAAC cost-effectiveness based on incremental costs per quality-adjusted life year (QALY). Two out of the eight identified studies considered NVAF patients with contraindications, for which the results suggest that, depending on the time horizon, LAAC is cost-effective compared with therapy with apixaban or aspirin or represents the dominant treatment alternative for patients with AF at risk of stroke and contraindications to (N)OACs (30, 31). Based on health economic modeling, Reddy et al. (30) found that LAAC was more clinically effective and, after a time horizon of eight years, also more cost-effective in this high-risk group. However, none of the aforementioned studies compared LAAC treatment with a control group, where treatments are not limited to those specific medications. Such a restriction does not reflect real-world standard care, which is relevant for economic evaluation from the perspectives of both SHI and society. Moreover, in Germany, no health economic evaluation has yet been conducted for the—potentially particularly effective—clinical use of LAAC in this specific high-risk population recruited in the CLOSURE-AF trial.

### Objective

1.2

In parallel to the CLOSURE-AF study, EvaClosure^3^ adds to previous evidence by comparing the LAAC procedure with best medical therapy prescribed by practitioners in a high-risk patient pool (including patients with potential contraindications to NOACs), evaluating its real-world health economic impact. EvaClosure uses both primary clinical study data and real-world German SHI claims data to analyze LAAC cost-effectiveness in comparison with currently available pharmaceutical alternatives. The incremental cost-effectiveness ratio (ICER) of the LAAC treatment is calculated using data from the different databases. A Markov model is used to further evaluate the health economic effects in a lifetime horizon. The model is parameterized with health-related quality-of-life effects (aggregated to QALYs) in the different study arms of the CLOSURE-AF study as well as direct and indirect costs estimated from SHI claims data, supplemented with patient-reported healthcare resource use and data from the literature.

In summary, EvaClosure aims to
assess resource utilization and medical costs associated with a high risk of stroke and bleeding in patients with AFassess direct and indirect costs in high-risk AF patients and of LAAC intervention vs. best medical careassess the utility effects (QALYs) of LAAC compared with best medical care in high-risk AF patientsevaluate the cost-effectiveness of the LAAC intervention compared with best medical care based on the ICER two and five years after intervention as well as in a life-time-horizon from the perspectives of both SHI and society.

## Methods

2

### Study design

2.1

EvaClosure is a longitudinal cohort study of adults with AF and high risk of stroke and bleeding, based on two independent study populations: an SHI claims data population and the EvaClosure population—a subpopulation of patients recruited in the CLOSURE-AF trial. There is no patient-individual linkage of the CLOSURE-AF trial data with the SHI claims data; however, since information from both data sources converge in the health economic evaluation, statistical matching is used to establish maximum similarity between both study populations.

Pseudonymized CLOSURE-AF trial data are used for matching, including study participants' demographic information (e.g., gender, age), medical history and comorbidities, therapy (treatment arm, medications), the CHA_2_DS_2_VASc and HAS-BLED scores, as well as periprocedural events, complications, and adverse events. A matched sample is drawn from the eligible SHI population, for which the utilization of healthcare services and corresponding costs are determined. The basis of data for the health economic evaluation and Markov modeling is supplemented by primary data on quality of life collected using the EQ-5D-5L instrument (33, 34) aggregated to QALYs, as well as information on further health resource usage captured by the validated and standardized FIMA^4^ questionnaire (35, 36) [modified version, see the section “Outcome measures and analyses” (A2) for details on the modifications]. The survey-based data are collected within the CLOSURE-AF trial every six months up to two years after patient inclusion.

### EvaClosure primary data

2.2

#### EvaClosure study population

2.2.1

The EvaClosure population comprises a subgroup of the CLOSURE-AF trial participants who consented to participate in the health economic evaluation (=EvaClosure study). Thus, the EvaClosure population includes both newly recruited patients and study participants who had already been enrolled in the CLOSURE-AF trial (see the section “trial data collection” for further details).

Patients enrolled in the CLOSURE-AF study do not have to meet any further criteria (apart from giving consent) to participate in the EvaClosure substudy. The eligibility criteria for CLOSURE-AF have been described elsewhere in detail (23); the trial includes patients 18 years or older with documented AF (paroxysmal, persistent, or permanent) and with high risk of bleeding or stroke. High risk of bleeding and stroke is determined by the CHA_2_DS_2_VASc and HAS-BLED scores as well as other characteristics [see (37, 38)]. Moreover, patients must be suitable candidates for catheter-interventional atrial appendage closure. Only those patients with an absolute contraindication to ASA and other antiplatelet drugs such as P2Y12-inhibitors like clopidogrel or with other comorbidities requiring long-term (N)OAC treatment were excluded from the study. Patients in the control group will be treated at the discretion of their local physician according to recommendations based on their specific bleeding risk. Patients will receive one of four approved NOAC treatments in different doses, including the relevant dose-reduction criteria: dabigatran, rivaroxaban, apixaban, or edoxaban. Table 1 summarizes the approved (N)OACs and doses. In case of contraindications to NOACs, patients may be either treated with vitamin-K antagonists (warfarin, phenprocoumon) and antiplatelet agents or there will be no stroke preventive treatment.

**Table 1 T1:** (N)OACs and approved/studied doses across indications.

(N)OACs	Higher dose	Lower dose
Dabigatran	150 mg BID (CrCl >30 mL/min)	110 mg BID [Age >80, Interacting drugs (e.g., verapamil), CrCl 15–30 mL/min]
Rivaroxaban	20 mg/d (CrCl >50 mL/min)	15 mg/d (CrCl 15-50 mL/min)
Apixaban	5 mg BID	2.5 mg BID (if two of the following present: age >80, weight <60 kg, serum creatinine >1.5 mg/dL)
Edoxaban	60 mg/d	30 mg/d (weight <60 kg, CrCl 15-50 mL/min)

BID = twice daily; CrCl, creatinine clearance.

#### EvaClosure sample size and recruitment

2.2.2

Within the health economic evaluation, the LAAC effect on health-related quality of life compared with standard therapy will be measured in terms of utilities; considering the duration of the underlying health conditions, these will be aggregated to QALYs. A two-sided, unpaired t-test (or Welch test) must be performed to ensure that differences in QALYs found between groups are not random. According to Freeman et al. (26), the utility value for the NOAC dabigatran is 0.994 and the 10% percentile is given as 0.975. Assuming a normal distribution, this results in a standard deviation of 0.015. In the same reference, the utility value for LAAC is reported as 0.998, while the 10% percentile of 0.994 results in a standard deviation of 0.003. In combination, assuming that both intervention and control groups are equally powerful, this results in an effect size of 0.37. With a targeted power of 85% and a significance level of 5%, this results in a case number of 264 patients (or 132 per group). Assuming a loss-to-follow-up-rate of 10%, the required sample size is 294 patients (147 per group). Recruitment for EvaClosure started in January 2021 and was completed in September 2023 when the target number of cases was reached. After enrollment, patients were followed up over a period of two years, with the data collection exercise completed in November 2024.

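### The 85% power for the QALY comparison is unsupported: its SDs come from therapy-level utilities and are implausible as between-patient SDs

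*Protocol article*

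**What the plan says.** Section 2.2.2 of the protocol article (EvaClosure sample size and recruitment) sets the purpose of the test: "A two-sided, unpaired t-test (or Welch test) must be performed to ensure that differences in QALYs found between groups are not random". The planning values come from reference 26. For control, "the utility value for the NOAC dabigatran is 0.994 and the 10% percentile is given as 0.975", and then "Assuming a normal distribution, this results in a standard deviation of 0.015". For the intervention, "the utility value for LAAC is reported as 0.998", and "the 10% percentile of 0.994 results in a standard deviation of 0.003". The two SDs are combined into an effect size of 0.37. The sample size follows: "With a targeted power of 85% and a significance level of 5%, this results in a case number of 264 patients", which is 132 per group, raised to 294 (147 per group) for 10% loss to follow-up.

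Section 1.1 shows what kind of source reference 26 is, since its number falls in this range: "Previous health economic evaluations of LAAC (25–32) predominantly considered patients with NVAF". Section 2.4.3 (module B1) applies the same unpaired t-test to QALYs derived from EQ-5D-5L responses. The population described in section 2.2.1 has AF with raised stroke and bleeding risk, and the control arm may receive a NOAC, a VKA, antiplatelet agents or no preventive treatment.

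**The concern.** An unpaired t-test on patient QALYs needs the spread of QALYs between patients. The article uses instead a spread inferred from a mean and a lower percentile quoted for each therapy. A mean of 0.994 with an SD of 0.015 describes a group in almost perfect health with hardly any variation, which does not fit the patients being enrolled. The planning control is also a single drug, whereas the actual control is a mix of treatments.

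The stated power depends directly on these SDs. If the true spread is several times larger, the study is far less able to detect a difference of 0.004 than the article says. A reader who trusts the 85% could then take a non-significant test as evidence that LAAC has no effect on utility. This is the only sample-size justification in the article.

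**Working it through.** **Inputs from section 2.2.2.** Means 0.994 and 0.998; 10% percentiles 0.975 and 0.994; two-sided alpha 5%; power 85%; 10% loss. Allocation is 1:1 (section 1.1).

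**1. Reproducing the plan.** Under normality, SD = (mean − 10% percentile) / 1.2816.
- Control: 0.019 / 1.2816 = 0.0148, stated as 0.015.
- LAAC: 0.004 / 1.2816 = 0.0031, stated as 0.003.
- Pooled SD = √((0.015² + 0.003²) / 2) = 0.0108.
- Difference = 0.998 − 0.994 = 0.004, so d = 0.004 / 0.0108 = 0.37.
- n per group = 2 (1.960 + 1.036)² / 0.37² = 131.2, rounded up to 132. The noncentral t gives 132.1, and power at 132 per group is 85.0%.
- 132 / 0.9 = 146.7, rounded up to 147 per group, 294 in total.

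Every stated figure is recovered. The fault is not in the arithmetic.

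**2. Can the SDs describe patients?** Take the assumed normal curves as distributions of patient utility, where 1.0 is full health.
- Share above 1.0, control: P(Z > 0.006 / 0.0148) = 34%.
- Share above 1.0, LAAC: P(Z > 0.002 / 0.0031) = 26%.
- Share of controls below 0.95: P(Z < −0.044 / 0.0148) = about 0.2%. For LAAC it is effectively zero.
- By the percentiles themselves, 90% of controls would score above 0.975 and 90% of LAAC patients above 0.994.

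This is not credible for EQ-5D-5L answers from AF patients at high stroke and bleeding risk.

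**3. What other SDs would imply.** The article gives no between-patient SD, so the SDs below are assumptions. The difference is held at the planned 0.004 with 132 per group. Then d = 0.004 / SD, the noncentrality is d × √(132 / 2), and power is from the two-sided noncentral t.

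| Assumed SD | d | Power for 0.004 | Difference detectable at 85% (0.37 × SD) |
|---|---|---|---|
| 0.0108 (as planned) | 0.37 | 85% | 0.004 |
| 0.02 | 0.20 | 37% | 0.007 |
| 0.03 | 0.13 | 19% | 0.011 |
| 0.05 | 0.08 | 9.9% | 0.019 |
| 0.10 | 0.04 | 6.2% | 0.037 |
| 0.15 | 0.027 | 5.5% | 0.056 |
| 0.20 | 0.02 | 5.3% | 0.074 |
| 0.25 | 0.016 | 5.2% | 0.093 |

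**4. On the two-year QALY scale.** A utility difference of 0.004 held for two years is 0.008 QALYs. With five equally spaced visits and trapezoid weights (0.25, 0.5, 0.5, 0.5, 0.25), the QALY variance is SD² × (4ρ + 0.875(1 − ρ)), where ρ is the within-patient correlation. At SD 0.10 and ρ = 0.5 the QALY SD is 0.156, d = 0.008 / 0.156 = 0.051, and power is 7.0%. Over assumed SDs of 0.10 to 0.30 and ρ of 0.5 to 1.0, power runs from 5.1% to 7.0%. Accumulating utilities into QALYs does not recover the stated power.

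**The case against.** The strongest objection is that these power figures mix scales. If 0.994 and 0.998 are not patient EQ-5D-5L scores, their difference of 0.004 is not an EQ-5D-5L effect either. Section 2.4.3 also counts QALYs from reduced mortality in the incremental total, and the Discussion expects gains from fewer strokes and bleeds and less medication. The true difference could exceed 0.004. This stands: the low figures are conditional on a difference taken from the same source as the SDs. A reader might infer that power is simply about 5%. The documents do not support that, because they give neither a between-patient SD nor an EQ-5D-5L effect size.

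Second, the source itself has not been seen. That its percentiles express uncertainty about a model parameter is an inference from their size, the ceiling at 1.0 and the company in which section 1.1 cites the source. Mass above 1.0 shows that the normal shape fails near the ceiling; a skewed, bounded distribution could share the same percentiles. This also stands, so the proper word is implausible, not impossible. It does not rescue the plan: a 10% percentile of 0.975 or 0.994 remains unrealistic for these patients whatever the shape.

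Third, a reader might infer that a non-significant t-test would block or distort the ICER. Nothing in the article says so. Section 2.4.4 computes the ICER from modules A2 and B1 without any condition on significance, and section 2.5 plans probabilistic sensitivity analyses.

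Finally, recruitment ended in September 2023 and data collection in November 2024, so the sample size cannot change. That limits the remedy to wording and reporting; it does not make the power claim correct.

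**Conclusion.** The point holds as a fault in the inputs. The 85% power is correctly calculated from SDs that are not credible for the outcome tested, and the article offers no other justification. Actual power is unknown. With the planned difference of 0.004 and 132 per group, it falls to 37% at an SD of only 0.02, and it is at or below about 6% for any SD of 0.10 or more. What the sample does support is 85% power for a standardized difference of 0.37. At an assumed SD of 0.10 to 0.25 this is about 0.037 to 0.093 utility points, roughly 9 to 23 times the planned difference. The use of one NOAC to represent a mixed control arm is a further, unquantified weakness of the same planning values.

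**What to change.** In section 2.2.2, withdraw the claim of 85% power for a 0.004 difference. State instead that 264 evaluable patients give 85% power for a standardized difference of 0.37, and translate this into utility or QALY units with a patient-level SD. Take that SD from EQ-5D-5L data already collected, pooled over arms and without arm labels. The SD of the two-year QALYs is preferable, because that is the variable tested; baseline scores alone would not give it. Until it is available, show the range of 0.037 to 0.093 utility points for SDs of 0.10 to 0.25, marked as an assumption.

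In section 2.4.3, report the QALY difference with its 95% CI beside the t-test, and say that a non-significant result is not evidence of equal utility.

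The cost is a rewritten paragraph, one added sentence and one blinded SD calculation. No extra patients are needed. The downside is a less favourable power statement.

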#### Trial data collection

2.2.3

Data collection on health-related quality of life within CLOSURE-AF began in March 2018 and ended in November 2024. Data on the use of health resources based on a modified version of the FIMA questionnaire^5^ were collected by standardized interviews conducted by a trained study nurse. Data were collected every 6 months and intended to cover a two-year period starting from baseline. According to the CLOSURE-AF study visit plan, patients were asked to complete the FIMA interview at baseline as well as at visit number V5–V8 (see Supplementary Table S2 in Supplementary Appendix A). Up to five observation points were planned for each patient, including baseline. Because the EvaClosure substudy started later than the main clinical trial, informed consent for some patients was obtained retrospectively starting from January 2021. For the retrospectively enrolled EvaClosure participants, the FIMA was used at the first possible visit. As a result, for patients who consented to EvaClosure at V8, that is 24 months after inclusion in the clinical trial, there was only one measurement point. For consecutively enrolled patients, a two-year follow-up with five measurement points was scheduled. An overview of the visit schedule and the respective data collected is provided in Supplementary Table S2 in Supplementary Appendix A.

